#### Inclusion criteria

Have suboptimally controlled diabetes at baseline. Suboptimally controlled diabetes is defined by a HbA1c level of 8.0% or greater. As such, patients will be required to have at least one of two HbA1c readings of 8.0% or greater in the past 6 monthsBe prescribed at least one oral diabetic medication for at least 3 monthsAged between 21 and 70 years of ageBe Singaporean citizens or permanent residentsBe able to converse in English or Mandarin

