#### Secondary outcomes

*Mean number of blood glucose days at month 6*. Up to three non-consecutive testing days during the last week of the intervention will be counted. This outcome corresponds to UC’s recommendations and to one of the goals that is incentivised in the process incentive arm
*Mean number of glucose readings that fall between 4 and 7 mmol/L at month 6*. This outcome is consistent with UC’s recommendations for blood glucose testing before meals. Consistent with the outcome incentive arm’s goal, only the first reading recorded on a maximum of three non-consecutive days will be taken into consideration during the last week of the intervention
*Mean number of medication-adherent days at month 6*. Medication-adherent days are defined as days where all medication doses were taken during pre-defined time windows as verified by the medication tracker. The number of medication-adherent days during the last week of the intervention will be calculated for each participant. This outcome corresponds to UC’s recommendation and to one of the goals that is incentivised in the process incentive arm
*Mean number of physically active days at month 6*. The number of days where the pedometer records at least 8000 steps during the last week of the intervention will be calculated for each participant. This outcome corresponds to UC’s recommendations and to one of the goals that is incentivised in the incentives arm.
*Mean cost of financial incentives at month 6.* This outcome will be calculated as the total contingent financial incentives earned by process incentive and outcome incentive arm participants during the last week of the intervention. This outcome will be used as part of the cost-effectiveness analysis
*Mean time taken by the intervention at month 6.* This outcome will be calculated as the total number of minutes spent by the CRC on adherence calculation and payment of financial incentives for process incentive and outcome incentive arms participants during the month-6 assessment. This outcome will be used as part of the cost-effectiveness analysis

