Each pedometer will be linked to an anonymous online Fitbit™ account that will be created for the study. The trial application will automatically synchronise with the Fitbit™ accounts and automatically update physical activity data for adherence and incentives calculations. This data will be checked regularly by the project coordinator to verify that the participants are synchronising their pedometer with their Fitbit™ account and that this data gets transmitted to the trial application. This is important because the pedometers can store up to 30 days of data. Participants who do not synchronise for 21 days will receive an automatic text message to remind them to synchronise. Participants who do not have access to a smartphone or personal computer will need to come to the polyclinic once a month where the CRC will synchronise their pedometers for them.

Paper-based survey questionnaires will be administered at baseline and month 6 by the CRC. Both questionnaires include the European Quality of Life-5 Dimensions-5 Levels,(EQ-5D-5L), BIPQ and BMQ survey instruments. The baseline survey also includes patient socioeconomic characteristics while the month-6 questionnaire contains questions on compliance with the medication tracker and medication-purchasing habits during the intervention period.

In addition, the CRC will complete participant checklists at baseline, months 3, 6 and 18. The Baseline checklist will include the participant’s current HbA1c reading and the date of the blood test. This information will be obtained from the SingHealth computerised patient database at Geylang Polyclinic. The randomisation code and study arm, the participants’ diabetes medication regimen, and whether the participants are new or current glucometer users will also be recorded on the checklist. The CRC will also confirm the participants have understood which study arm they have been randomised to, record the response on the checklist and explain again if necessary.

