### Statistical methods

#### Primary analysis

Change from baseline in HbA1c levels at month-6 will be linearly regressed on (1) binary variables indicating the intervention arms with UC as a reference category, (2) baseline HbA1c levels, (3) a binary variable indicating titration change and (4) other baseline characteristics (gender, age, language spoken, education, occupation, income, EQ-5D-5L, BIPQ, SMBG, BMQ and DSCA scores, and binary variables indicating comorbidities) in order to increase statistical efficiency. The analysis will be performed according to an intention-to-treat approach. All missing data will be imputed using Markov chain Monte Carlo multiple imputation. To test the robustness of the results, we will carry forward the last measured HbA1c level (baseline or month 3) for those participants who withdraw from the study as those intervention participants who do not achieve their goals might disproportionally withdraw from the study. The last measured HbA1c level will also be carried forward for those participants who are discontinued from the study after switching from oral to insulin therapy.

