#### Secondary analyses

The number of blood glucose testing days, glucose readings within acceptable range, medication-adherent days, and physically active days at month 6 will be linearly regressed on binary variables indicating the intervention arms and on the same baseline characteristics as for the primary analysis. If the interventions show statistically significant improvements in HbA1c levels, we will conduct a cost-effectiveness analysis for both intervention arms. The perspective of the cost-effectiveness analysis will be that of the health system. Effectiveness will be measured by the primary outcome and costs will include the average financial incentives paid, labour costs associated to the administration of the incentives, and the cost of devices. The incremental cost-effectiveness ratio between each intervention and UC will be calculated and compared to those of other interventions aiming at reducing HbA1c levels.

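### The covariate list omits the baseline medication regimen, which is recorded and affects how hard an adherent day is to achieve, so the medication-adherent-days comparison loses a little precision

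*Protocol article*

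**What the plan says.** All references are to the protocol article.

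- **Statistical methods, Primary analysis.** Besides the arm indicators, the model contains "2) baseline HbA1c levels, (3) a binary variable indicating titration change and (4) other baseline characteristics". The last group is spelled out as "other baseline characteristics (gender, age, language spoken, education, occupation, income, EQ-5D-5L, BIPQ, SMBG, BMQ and DSCA scores, and binary variables indicating comorbidities", and its stated purpose is statistical efficiency. The list has no item for the medication regimen at baseline. The titration item records a change in treatment, not the starting regimen.
- **Secondary analyses.** The number of medication-adherent days at month 6 is regressed on the arm indicators and "on the same baseline characteristics as for the primary analysis".
- **Secondary outcomes.** "Medication-adherent days are defined as days where all medication doses were taken during pre-defined time windows". The count covers the last week of the intervention, so it runs from 0 to 7.
- **Arm 2: Process incentive.** The worked example has a breakfast and a dinner window, and both must hold a logged reading for the day to count.
- **Data collection.** On the baseline checklist, "the participants’ diabetes medication regimen, and whether the participants are new or current glucometer users will also be recorded on the checklist".
- **Randomisation.** The only blocking factor is current versus new glucometer use, so the regimen is balanced across arms by chance alone.

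**The concern.** The article gives a reason for its covariates, a gain in efficiency, so the list can be judged against that aim. For medication-adherent days, the outcome definition itself points to a likely predictor: the number of windows that must all be met each day. That number follows from the prescribed regimen, is fixed before allocation if taken from the baseline record, and comes from data the site already collects. The list nevertheless consists of sociodemographic items, questionnaire scores and comorbidities.

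At stake is the width of the confidence interval for one secondary outcome. Variation between participants that reflects only how many windows they were given stays in the residual, although it could be removed at almost no cost.

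**Working it through.** **1. Does any stated figure depend on the covariates?** The Sample size section gives a standard deviation of 2, a difference of 1 percentage point, significance level 2.5% (taken as two-sided) and 80% power.

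- Per incentive arm: n = 2 × 2² × (2.2414 + 0.8416)² / 1² = 8 × 9.505 = 76.04, against 76 stated.
- UC arm: 1/n = 1/(4 × 9.505) − 1/152 = 0.02630 − 0.00658 = 0.01972, so n = 50.7, against 51 stated.

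Both figures reproduce from an unadjusted standard deviation. The planned power takes no credit for covariates, so the omission makes no stated number wrong.

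**2. How much could the number of windows explain?** The documents give no dosing split, per-dose probability or variance for this outcome. The following are assumptions:

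- 30%, 50% and 20% of participants have one, two and three daily windows;
- each window is met independently with probability p, between 0.70 and 0.85, the same for all regimens;
- the total standard deviation of adherent days is 2.4, a variance of 5.76.

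Expected adherent days with k windows are 7 × p^k.

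| p | k = 1 | k = 2 | k = 3 | Weighted mean |
|---|---|---|---|---|
| 0.85 | 5.95 | 5.06 | 4.30 | 5.17 |
| 0.70 | 4.90 | 3.43 | 2.40 | 3.67 |

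The between-regimen variance is the weighted sum of squared deviations from the mean:

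- p = 0.85: 0.3 × 0.776² + 0.5 × 0.116² + 0.2 × 0.875² = 0.34
- p = 0.70: 0.3 × 1.235² + 0.5 × 0.235² + 0.2 × 1.264² = 0.80

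Share of variance explained: 0.34/5.76 = 5.9% and 0.80/5.76 = 14%.

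**3. Effect on the standard error.** The ratio of adjusted to unadjusted standard error is √(1 − share): √0.941 = 0.970 and √0.860 = 0.927. The reduction is about 3% to 7%. For UC against one incentive arm at the planned 60 and 90, the unadjusted standard error is 2.4 × √(1/60 + 1/90) = 0.400 days. Adjusted, it is 0.388 to 0.371 days.

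**4. Sensitivity to the assumed standard deviation.** A count from 0 to 7 cannot have a population standard deviation above 3.5. At that ceiling (variance 12.25) the shares are 0.34/12.25 = 2.8% and 0.80/12.25 = 6.6%, and the standard error falls by 1.4% to 3.3%. The gain would also shrink if most participants shared one dosing frequency, if people with more windows were more reliable per dose, or if regimens changed between baseline and month 6.

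**5. Size of chance imbalance.** For arms of 60 and 90, the standard deviation of the difference in adherent days due to regimen imbalance alone is √(0.34 × (1/60 + 1/90)) = 0.10 to √(0.80 × (1/60 + 1/90)) = 0.15 days out of 7.

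**The case against.** The strongest reply is that the article prespecifies a reasonable adjusted model, that no covariate list is complete, and that every input to the 6-14% is assumed. The gain concerns one secondary outcome. All of this stands, and it keeps the point at the level of an optional refinement. It does not remove the point, because the article itself fixes the list, gives efficiency as its purpose, and defines an outcome that depends on the omitted variable.

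Three stronger readings are tempting, and the documents do not support them.

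- **A reader might infer bias.** In a randomised comparison analysed by linear regression, leaving out a prognostic baseline variable costs precision but does not bias the arm difference. A chance imbalance of 0.10 to 0.15 days is already covered by the unadjusted standard error.
- **A reader might infer that the HbA1c model also wastes available data,** since eligibility requires "at least one of two HbA1c readings of 8.0% or greater in the past 6" months. But baseline HbA1c is already the second covariate. The earlier readings appear only as an eligibility check, and the checklist records a single current reading, which may itself be a qualifying one. The article does not show that a separate earlier value is recorded for analysis. The added gain may also be nil: with correlations of 0.8 (earlier with baseline), 0.5 (baseline with month 6) and 0.40 (earlier with month 6), the partial correlation is proportional to 0.40 − 0.5 × 0.8 = 0.
- **A reader might infer that the regimen strongly predicts HbA1c change.** No figure in the article speaks to that.

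**Conclusion.** The point holds for the baseline medication regimen, chiefly in the medication-adherent-days model. The regimen is collected, the outcome definition depends on it, and the covariate list leaves it out. Under the stated assumptions on dosing split, per-dose probability, independence and a standard deviation of 2.4 days, adjustment would explain about 6-14% of the variance and reduce the standard error by roughly 3-7%. With a larger true standard deviation or less varied regimens the gain would be smaller. For the HbA1c model, any gain from the number of oral drugs is unquantified. The validity of the planned comparisons and the stated sample sizes are unaffected. This is a minor, low-cost improvement.

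**What to change.** Prespecify the number of daily dosing windows, derived from the regimen recorded at baseline, as a covariate in the medication-adherent-days model. State whether it enters as a linear term or as categories. Use the baseline value and not the regimen at month 3 or 6, because later changes come after randomisation. The number of oral diabetes drugs at baseline may be added to the HbA1c model as an option. The testing-days and active-days models need no change on this ground.

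The cost is one or two degrees of freedom in a trial of 240, plus coding a variable from a checklist already completed. According to Trial status, 140 of the 240 participants had been enrolled and recruitment was ongoing, so the change could be written in before the final analysis.

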### Participant timeline and study arms

Participants in all three study arms will be issued with one Fitbit Zip™ and one eCAP™. A Fitbit Zip™ (Fitbit Inc., San Francisco, CA, USA) is a pedometer with wireless synchronisation to smartphones and computers. It tracks daily steps taken, calories burned and distance walked. An eCAP™ (Information Mediary Corporation, Ottawa, ON, Canada) is a medication-event monitoring system with an inbuilt electronic tag which records the time whenever it is closed. Participants will also use a glucometer for the study. A glucometer is a medical device that measures blood glucose levels. It is estimated that approximately half of the study participants will already use a glucometer before joining the study. Participants without a glucometer will be provided with a Nipro TRUEresult™ glucometer which they may keep after the study ends. The project coordinator will label the study devices with the participant’s unique ID number as allocated at randomisation. The clinical research coordinator (CRC) will demonstrate how to adequately use all study devices. Participants who have difficulties with their glucometer will be referred to a health counsellor at the polyclinic. Participants in all study arms will attend baseline, month 3 and month 6 assessments. At the baseline and month-6 assessments, the participants will fill out survey questionnaires (see the ‘Data collection’ section below) and take HbA1c blood tests. At the month-3 and month-6 assessments, the CRC will use the data from the three study devices to evaluate treatment adherence and the corresponding incentive payments in supermarket vouchers when applicable. At the month-18 assessment, a month-18 checklist based on participants’ medical records will be filled up by the CRC. Participants’ HbA1c blood test result since their month-6 assessment and any change in diabetes medication regimen (e.g. initiation of insulin) will be recorded. Figure 2 displays the timeline of the participants in the study.

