#### Explanatory outcomes

*Mean change from baseline in glycated haemoglobin HbA1c at months 12 and 18*

*Proportion of participants whose oral medication was titrated up at months 6, 12 and 18*

*Proportion of participants who switched to insulin therapy at months 6, 12 and 18*

*Mean change from baseline in EQ-5D-5L* [21] *score at month 6* as a measure of functional health status. This scale has been validated in people with type-2 diabetes [22]. In Singapore, both the English and Mandarin versions have been validated in people with cancer [23]
*Mean change from baseline in Brief Illness Perception Questionnaire* [24] *(BIPQ) score at month 6*. This scale has been validated in English for multiple health conditions including diabetes [25]. The Mandarin version has been validated in Taiwan in people with coronary heart disease [26]
*Mean change from baseline in Self-Monitoring of Blood Glucose* [27] *(SMBG) score at month 6*. This scale has been validated in English in people with type-2 diabetes but has yet to be validated in Mandarin and in Singapore
*Mean change from baseline in general and specific scores of the* Beliefs about Medication Questionnaire [28] *(BMQ) at month 6*. The English version of the scale has been validated for several chronic diseases including diabetes [29] while the Mandarin version has been validated in other settings such as after mechanical heart-valve replacement [30] and depression [31]. Validity in Singapore has not been established for this scale
*Mean change from baseline in the exercise subscale of the Diabetes Self-Care Activities* [32] *(DSCA) at month 6.* The English version of the scale has been pretested for acceptability and comprehensibility in a study involving people with type-2 diabetes [32] but has neither been pretested in Mandarin nor in Singapore

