### Randomisation

Prior to the start of recruitment, randomisation numbers will be generated by the principal investigator of the study and the project coordinator using Stata 13.2 to create an assignment schedule for block-randomisation to allocate eligible participants into one of the three study arms in a ratio of 2:3:3. Whether participants are current glucometer users or not (current vs. new glucometer users) will be used as the blocking factor, and the block size will not be communicated to study site in order to minimise the predictability of the random sequence. The project coordinator and the principal investigator of the study will then store the assignment schedule (including generation information) on a secure server at Duke-NUS. For allocation concealment, the project coordinator and a witness external to the study will enclose the assignments in sequentially numbered, opaque, sealed, randomisation envelopes and the project coordinator will hand these to the CRC along with other relevant study materials. Note that the behavioural nature of the intervention precludes masking the arm allocation to both the study team and participants. The allocation will be revealed to both the CRC and participant upon enrolment. However, the study arm assignment will be not be revealed to the laboratory staff assessing the primary outcome (HbA1c test).

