### Explanatory analyses

The same model as for the primary analysis will be conducted with changes from baseline in HbA1c levels at months 12 and 18. Logistic regressions of binary variables indicating whether the participants have had a titration change of their oral medicine, and whether they have switched to insulin therapy at months 6, 12 and 18 will be estimated. Linear regressions of the changes from baseline in EQ-5D-5L, BIPQ, SMBG, BMQ and DSCA scores at month 6 will also be estimated. For all models, the covariates will be binary variables indicating the intervention arms and the same other baseline characteristics as for the primary analysis. Next, the models used in the primary and secondary analyses will be extended by adding interaction terms between potential intervention moderators (gender, age, language spoken, education, occupation, income, EQ-5D-5L, BIPQ, SMBG, BMQ and DSCA scores, and binary variables indicating comorbidities) and the binary variables indicating study arms. In particular, this analysis will be used to determine the benefit incidence of the intervention according to socioeconomic factors.

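### The blocking factor, current versus new glucometer use, is absent from the stated covariates of the regression models; linear-model standard errors are then conservative to the extent that it is prognostic

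*Protocol article*

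**What the plan says.** The Randomisation section of the protocol article states: "Whether participants are current glucometer users or not (current vs. new glucometer users) will be used as the blocking factor". The Abstract and the Trial design section name the same factor. The section on participant timeline and study arms expects that "approximately half of the study participants will already use a glucometer before joining the study". The Data collection section describes the baseline checklist and says that "whether the participants are new or current glucometer users will also be recorded on the checklist".

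Under Primary analysis, change in HbA1c at month 6 is regressed linearly on arm indicators, baseline HbA1c, a titration-change indicator and further baseline characteristics, which are itemised as "gender, age, language spoken, education, occupation, income, EQ-5D-5L, BIPQ, SMBG, BMQ and DSCA scores, and binary variables indicating comorbidities". The stated aim of these covariates is efficiency. Glucometer status is not among them.

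The other models take over the list. The secondary outcomes are regressed on arm and "on the same baseline characteristics as for the primary analysis". For the explanatory models, "the covariates will be binary variables indicating the intervention arms and the same other baseline characteristics as for the primary analysis". Not all of these are linear: the plan includes "Logistic regressions of binary variables indicating whether the participants have had a titration change of their oral medicine", and the same for a switch to insulin. The moderator list under Explanatory analyses repeats the same items, again without glucometer status.

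The SMBG item does not stand in for the factor. It is a questionnaire score, described under Explanatory outcomes: "This scale has been validated in English in people with type-2 diabetes but has yet to be validated in Mandarin and in Singapore". No section says that the analysis adjusts for the blocking factor or stratifies by it.

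**The concern.** Blocking within glucometer status balances the arms on it, so differences between the two strata drop out of the arm contrast. A linear model without the factor still counts those differences as residual variation. If the strata differ in outcome, the reported SE then exceeds the true spread of the estimate, confidence intervals are wider than they need be, and tests reject less often than their nominal level.

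What is at stake is the reported precision that the blocking should have brought. The outcomes most exposed are the number of testing days and the number of in-range readings. Both are read from the glucometer, so whether a participant already used one has a more direct link to them than to HbA1c.

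**Working it through.** **The plan's own figure.** The Sample size section uses a difference of 1, SD 2, a significance level of 2.5% and 80% power. Taking the test as two-sided:

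- Per intervention arm: n = 2 × 2² × (2.2414 + 0.8416)² / 1² = 76.04 (stated: 76).
- Usual care against 152 pooled: 1/n = 1/[4 × (2.2414 + 0.8416)²] − 1/152, so n = 50.7 (stated: 51).

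Both reproduce. Neither depends on the covariate list, so they do not bear on this point.

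**Linear models: formula.** Let p be the share of current users and D the between-stratum difference in outcome, in residual SDs, that remains after the listed covariates. With arms balanced within strata, leaving the factor out adds p(1 − p)D² to the residual variance, in units of the residual variance:

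SE without the factor / SE with it = √(1 + p(1 − p)D²).

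The article's expectation of about half gives p = 0.5 and p(1 − p) = 0.25, the largest possible value; unequal strata give less. D is not in the article, so the range 0 to 1 is an assumption.

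**Consequences for the outcome-versus-process comparison of HbA1c.**

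- Actual two-sided error at nominal 0.025: 2 × [1 − Φ(2.2414 × ratio)].
- Power: 90 less 20% leaves 72 per arm. With SD 2 taken as the residual SD (an assumption), 1/[2 × √(2/72)] = 3, so power = Φ(3 − 2.2414 × ratio).

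| D (assumed) | SE ratio | Actual error at nominal 0.025 | Power, factor omitted |
|---|---|---|---|
| 0 | 1.000 | 0.0250 | 77.6% |
| 0.2 | √1.01 = 1.005 | 0.0243 | 77.3% |
| 0.5 | √1.0625 = 1.031 | 0.0209 | 75.5% |
| 1 | √1.25 = 1.118 | 0.0122 | 68.9% |

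With the factor in the model, power is 77.6% in every row.

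**Check by simulation.** 240 participants, two equal strata, 2:3:3 permuted blocks of 8 (block size assumed), residual SD 2, 4,000 runs, outcome-versus-process contrast:

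| D | True SD of estimate | Mean reported SE, factor omitted | Mean reported SE, factor included |
|---|---|---|---|
| 0 | 0.296 | 0.297 | 0.297 |
| 0.2 | 0.298 | 0.300 | 0.298 |
| 0.5 | 0.299 | 0.307 | 0.298 |
| 1 | 0.302 | 0.334 | 0.298 |

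The true spread was the same with and without the factor. Only the reported SE changes.

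**Logistic models.** A separate simulation (2,400 participants, 600 runs, stratum log-odds difference 1.0, true arm coefficient −0.5) gave a mean coefficient of −0.477 without the factor and −0.504 with it. The mean SEs were 0.112 and 0.115. Omission moves the coefficient toward zero and makes the SE slightly smaller.

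**The case against.** The strongest objection is that the cost depends wholly on D, and the article gives no figure for it. The primary model already holds baseline HbA1c, the SMBG and DSCA scores and socioeconomic factors, so what glucometer status adds for HbA1c may be close to nothing. Even for the testing outcomes, those without a glucometer receive one, use of the devices is demonstrated, and all arms are advised to test on three days a week. The outcome is capped at three days in the last week of a six-month intervention, by which time current and new users may have converged. Finally, the error is in the safe direction: linear-model estimates are unbiased and false-positive rates fall rather than rise.

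All of this stands as a limit on size. D = 1 is an illustration and not a finding about this trial, and small values of D belong in the range. It does not remove the point. The article's list is specific, down to occupation and five questionnaire scores, and its stated purpose is efficiency. A list that detailed is a choice, not something condensed away, and it leaves out the one variable used to constrain the randomisation.

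**Conclusion.** The omission is certain on the text. Its consequence is conditional: in the linear models, reported SEs are conservative by 0% at D = 0, about 0.5% at D = 0.2, 3% at D = 0.5 and 12% at D = 1. This assumes equal strata and balance within them. For HbA1c the lower values are the more likely; for testing days and in-range readings a larger D is plausible but undocumented. This is a low-cost improvement and not a threat to validity.

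A reader might infer three stronger things, none of which the article supports:

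- That SEs are too large in every model. They are not if the factor adds nothing to the listed covariates, and in the logistic models the effect is attenuation of the coefficient.
- That the trial's effect estimates are biased or its positive findings unsafe. The linear-model estimates are unbiased and the tests err toward caution.
- That the imputation model also lacks the factor. The article names the imputation method but lists no variables for it, so no omission is shown there.

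**What to change.** Add the current/new glucometer indicator as a fixed covariate in the primary, secondary and explanatory regression models, both linear and logistic. One sentence under Primary analysis would do this, because the other sections refer back to that list. The cost is one degree of freedom and no new data, since the baseline checklist already holds the variable. If the factor turns out not to be prognostic, essentially nothing is lost.
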